## Abstract

**Background:**

Postoperative pancreatic fistula after pancreatoduodenectomy is a much-feared complication associated with substantial mortality and morbidity. The current standard for diagnosing postoperative pancreatic fistula, besides routine clinical examination, include radiological examinations, analysis of pancreatic drain amylase activity, and routine blood samples. Another promising method is by intraperitoneal microdialysis to monitor intraperitoneal metabolites measured at the pancreaticojejunostomy, thereby detecting what occurs locally, before chemical events can be reflected as measurable changes in systemic blood levels.

**Methods:**

The MINIMUM study is a prospective, randomized, controlled, single center enrolling 200 patients scheduled for open pancreatoduodenectomy comparing the microdialysis method to the “standard of care.” Half of the included patients will be randomized to receive an intraperitoneal microdialysis catheter implanted at the end of surgery and will be monitored by microdialysis as an additional monitoring tool. The other half of the patients will not receive a microdialysis catheter and will be monitored according to the current standard of care. The primary objective is to evaluate if the microdialysis method can reduce the total length of stay at the hospital. Secondary endpoints are the frequency of complications, length of stay at the hospital at our institution, catheter malfunction, number of infections and bleeding episodes caused by the microdialysis catheter, patient-reported quality of life and pain, and cost per patient undergoing pancreatoduodenectomy. The patients will be randomized in a 1:1 ratio.

**Discussion:**

Intraabdominal microdialysis could potentially reduce morbidity and mortality after pancreatoduodenectomy. Furthermore, there is a great potential for shortening the in-hospital length of stay and reducing the financial aspect considerably. This study may potentially open the possibility for using microdialysis as standard monitoring in patients undergoing pancreatoduodenectomy. The hypothesis is that the microdialysis method compared to “standard care” will reduce the total length of hospital stay.

**Trial registration:**

Clinicaltrials.gov (NCT03631173). Registered on 7 September 2018 under the name: “Monitoring of patients With Microdialysis Following Pancreaticoduodenectomy”. Based on protocol version 19-1, dated 15th January 2019.

**Supplementary Information:**

The online version contains supplementary material available at 10.1186/s13063-021-05221-9.

## Background and rationale

### Pancreatoduodenectomy and postoperative pancreatic fistula (POPF)

Pancreatoduodenectomy is the treatment of choice for tumors of the periampullary region. Due to its high-risk nature, pancreatoduodenectomy has become a routine procedure in specialized high-volume centers, and mortality has decreased significantly over the last decades. To achieve better results, several factors have been identified and improved upon; pre-and postoperative management, appropriate selection of patients, improved surgical tools and skills, and the development of multidisciplinary teams [1, 2]. However, even if mortality is less than 3–5% in experienced hands, the overall morbidity rate is still high—from 30% to 50%—leading to prolonged in-hospital stay and increased costs [3]. There are 3 different anastomoses (surgical connection between two structures) with the potential for a leak post-pancreatoduodenectomy; the gastrojejunostomy, choledochojejunostomy, and the pancreaticojejunostomy. An anastomotic leakage after pancreatoduodenectomy is a feared complication with substantial mortality and morbidity. Formation of a postoperative pancreatic fistula (POPF) is a serious complication. Pancreatic secretions with its eroding enzymes like proteases and lipases erode surrounding tissues and lead to partial or complete anastomotic dehiscence and break-down of surrounding tissue. In addition, the leakage of pancreatic secretions, through a fistula in the pancreatico-enteric anastomosis can cause inflammation and auto-destruction of the peripancreatic and retroperitoneal tissues as well as the surrounding vessels and viscera. Subsequently, this can lead to delayed gastric emptying, biliary leakage, development of vascular erosions and hemorrhage, and lastly intra-abdominal abscesses. These may all lead to sepsis, shock, multiorgan failure, and death [3]. The incidence of POPF is reported to lie between 0% and 36% in older reports, but it tends to be much lower in high-volume centers and newer reports. Still, the most recent incidence of POPF after pancreatoduodenectomy is in the range of 20–25% [4–7]. The largest contributor to the postoperative mortality is due to these complications.

The treatment of POPF can be difficult and management may range from simple observation with or without percutaneous drainage, to the urgent reoperation and management of abdominal sepsis with organ failure and prolonged intensive care [7]. Clinically, POPF is divided into two severity grades (B or C) [8]. The risk of death and severe morbidity increases considerably from a biochemical leakage to a POPF grade C. Studies have shown that the cost associated with a patient with a fistula is 1.3–6 times that of a patient with no complications after pancreatoduodenectomy [9, 10].

The current standard for diagnosing POPF involves, alongside bedside clinical examination, the analysis of pancreatic amylase activity from intraabdominal drains and routine blood samples, and radiological imaging if pathology is suspected. A novel method is intraperitoneal microdialysis to monitor intraperitoneal metabolites (glycerol, lactate, pyruvate, and glucose) measured at the pancreaticojejunostomy.

### Microdialysis

A microdialysis catheter is constructed as a concentric tube where a perfusion fluid enters through an inner tube, flows to its distal end, exits the tube, where the exchange between the intraperitoneal fluid and the perfusion fluid takes place. The perfusate equilibrates with molecules in the intraperitoneal fluid. Thereafter the fluid enters the space between the inner tube and the outer dialysis membrane and the direction of flow is now reversed. The fluid moves toward the proximal end of the catheter and is finally collected in a microvial. Microdialysis is a technique to monitor the chemistry of the extracellular space in near real-time, thereby detecting what occurs locally, before chemical events can be reflected as measurable changes in systemic blood levels.

The microdialysis technique monitors substances produced by the products of cell metabolism. Microdialysis is a technique that has been utilized extensively in fields of plastic surgery and neurosurgery among others. Few studies with intraperitoneal microdialysis have been performed, but these are few in numbers and include few patients [11–17]. A small number of studies have investigated the use of microdialysis related to leakage from anastomosis between bile and pancreatic ducts. Intraperitoneal microdialysis will be investigated as a method to detect anastomotic leakage earlier than clinical signs appear. End-organ monitoring with microdialysis catheters with regular measurements of lactate, pyruvate, glucose, and glycerol has been shown to be a sensitive and safe method of detection of circulatory disorder in, i.e., liver transplants and colon anastomoses [16, 18]. During periods of ischemia, metabolic changes can be observed in the perianastomotic areas by increases in lactate, reduction of glucose, and an increase of lactate-to-pyruvate (L/P) ratio. A study by Ansorge et al. [19] showed that patients with a POPF had higher intraperitoneal glycerol concentrations and lactate/pyruvate ratios, and lower glucose concentrations. Other studies [11–28] have demonstrated that intraperitoneal microdialysis is a promising tool for the early detection of anastomotic leakage and intraabdominal pathology in patients undergoing abdominal surgery, but these studies have been small and not randomized. As to the best of our knowledge, there are currently no randomized studies that have looked at microdialysis as a method of detecting anastomotic leakage after pancreatic surgery. Monitoring immediately after surgery in patients undergoing pancreatoduodenectomy may provide an advantage by allowing for prompt interventions. Consequently, this may reduce the total length of stay (LOS) at the hospital. Therefore, further adequately powered randomized trials are needed.

## Methods/design

Our hypothesis is that the microdialysis method compared to “standard care” will reduce the total length of hospital stay.

### Objectives and endpoints

Our primary objective is to evaluate if the microdialysis method will reduce the total LOS at the hospital in patients undergoing pancreatoduodenectomy. The primary and secondary objectives combined with the primary, secondary, and other explorative endpoints and how they are assessed are presented in Table 1.

**Table 1 Tab1:** Primary and secondary objective. Primary, secondary, and other explorative endpoints and how they are assessed

Objectives		Endpoints	Assessments
Primary	To evaluate if the microdialysis method will reduce the total length of stay at the hospital(s).	Number of days/hours from end of surgery to hospital discharge from primary hospital plus number of days/hours for subsequent admissions with a diagnosis associated with the primary surgery at any hospital	Hours/days from the initial operation (end of surgery) to hospital discharge. All hospitals admitting the patient are included, also transferred hospitals. From electronic patient records.
Secondary 1	To evaluate predictive score systems for POPF	Occurrence of POPF	POPF defined according to the definition of the ISGPF. Graded into “biochemical”, B or C. From medical record, CT-scans. The following risk factors will be assessed: Age, gender, smoking history—current and package years, preoperative BMI, weight loss, Intraabdominal fat thickness, pancreatitis history, relation to portal vein to tumor, primary diagnosis, radiological (assessed by CT-scan) PD width, intraoperative PD width, intraoperative blood loss, pancreatic texture, pancreatic fat, pancreatic fibrosis, drain amylase. From preoperative examination, medical record, CT-scan, during surgery and postoperative examinations.
Secondary 2	To evaluate if microdialysis data contribute to reduced length of stay at the primary hospital and ICU	Length of stay at the primary hospital Length of stay at the ICU	Number of days/hours from end of initial operation to primary hospital discharge and hours admitted at the ICU. From electronic patient records.
Secondary 3	To evaluate if there is a special pattern of inflammatory markers in the microdialysate and serum in patients with/without POPF	Concentration of inflammatory markers	From laboratory analysis
Secondary 4	To evaluate the reliability and complications using microdialysis catheter CMA 65	Occurrence of catheter malfunction Occurrence of bleedings and infections	Daily check of the microdialysis catheter is functioning. Assessments of bleeding which affects circulatory parameter (development of circulatory shock or need of transfusion) and infection
Secondary 5	To evaluate patient quality of life and pain	Overall score and sub-scale scores of patient-reported questionnaires	Two patient-reported questionnaires: “Abdominal surgery impact scale” will be gathered with patient-reported McGill Pain Questionnaire-2 (SF-MPQ-2) preoperatively, at POD3 ± 1 day and at discharge ± 2 days from primary hospital + 30 and 90 days after surgery.
Secondary 6	To compare hospital costs of using microdialysisis versus “standard of care”	Number of Euros per patient undergoing PD based on microdialysis costs, length of stay (ICU and inpatient stay), reoperations, and postoperative complications	From medical records, procedures noted in electronic patient records, and radiological electronic patient records.
Exploratory	To compare other endpoints between patient with and without a microdialysis catheter	Hours from end of surgery to diagnosis of postoperative pancreatic AL (grades B and C).	Time as noted in electronic patient records.
		Total quantity (μg/mg) of vasoactive medications during surgery	Amount during surgery where the PD was performed. Derived from electronic patient records.
		Fluid balance - total iv volume administered and total diuresis	Diuresis and amount of fluid given iv during surgery and postoperatively until discharge from the hospital where the PD was performed. Derived from electronic patient records.
		Number of patients with biliary fistula	Biliary fistula defined according to the definition of the International Study Group of Liver Surgery (ISGLS). Graded into A, B, or C. From medical record, CT-scans.
		Number of patients with gastro-enteric AL	Gastro-enteric AL. From medical record, CT-scans.
		Pancreatic amylase and bilirubin concentrations in drainage fluid and in serum.	Analysis of drainage fluid and serum
		White blood cell count, C-reactive protein; concentrations	Laboratory data
		Number of patients with postoperative complications during total hospital stay in total and per complication	Defined by the modified Clavien-Dindo classification, from medical record, radiological examinations, and electronic patient records.
		Patient’s discharge disposition	From electronic patient records.

*AL* anastomotic leakage, *BMI* body mass index, *CT* computed tomography, *ICU* intensive care unit, *ISGLS* International Study Group of Liver Surgery, *ISGPF* International Study Group on Pancreatic Fistula, *iv* intravenous, *PD* pancreatoduodenectomy, *POD* postoperative day, *POPF* postoperative pancreatic fistula

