**Histological assessment**							
**Pancreatic fat**			X				
**Pancreatic fibrosis**			X				
**Drain tube**			Insertion	Cessation POD 1–3 (or more) unless the effluent is bile, enteric stained or turbid or depending on microdialysis concentrations			
**Amylase and bilirubin in drain fluid**				At POD 1–3 and on indication thereafter if drain still in place			
**Pantoperazole 40 mg iv**				Administered daily for 7 days			
**Sampling/analyzing microdialysate**				Every hour in the first 24 h. Thereafter, every two hours until POD 2. From POD 2: every 4th hour until discharge; Pyruvate, lactate, glucose, glycerol			
**Collecting microdialysate for cytokines**				Twice daily (≈ 08.00 am and 08.00 pm)			
**Microdialysis catheter function and duration**			X	X			
**Abdominal CT scan during admission(s)**				POD 2 in patient with high microdialysate concentrations in three consecutive microdialysate samples and/or at the surgeon's discretion	at the surgeons discretion	at the surgeons discretion	at the surgeons discretion
**Postoperative complications - Clavien-Dindo classification ≥ 2**				X	X	X	X
**Time from end of surgery to a diagnosed anastomosis leakage, if applicable**				X	X	X	X
**Type of complications**				X	X	X	X
**Type of procedures due to complications**				X	X	X	X
**Cost of complications**				X	X	X	X
**Transfer(s) to ICU**				X	X	X	X
**LOS at primary hospital and ICU**				X	X	X	X
**LOS at secondary hospital**						X	X
**Mortality**			X	X	X	X	X

*ALAT* alanine aminotransferase, *ALP* alkaline phosphatase, *ASAT* aspartate aminotransferase, *BMI* body mass index, *CRP* c*-*reactive protein, *CT* computed tomography, *GFR* glomerular filtration rate, *GGT* gamma*-*glutamyl transferase, *Hb* hemoglobin, *ICU* intensive care unit, *LD* lactate dehydrogenase, *LOS* length of stay, *PBW* predicted body weight, *PD* pancreatic duct, *POD* postoperative day, *SpO2* peripheral oxygen saturation, *TNM* tumor-nodule-metastasis, *Trc* platelets, *WBC* white blood cells

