### Miscellaneous data to be collected

All data will be plotted in a password-protected web-based eCRF (Viedoc™, PCG Solutions, [name]) consecutively by the study team (investigators and study nurses).

Baseline demographic data, current medication, and the presence of any chronic diseases will be collected. Intraoperative data and postoperative complications, as defined by the modified Clavien-Dindo classification, will be recorded until POD 90. Total hospital stay + LOS at the hospital/ICU, pre- and postoperative CT-scan results, mode of nutrition, and any transfusion requirements will also be recorded. Sequential Organ Failure Assessment scoring (SOFA) will be performed preoperatively, and up to POD 10 if the patient is still admitted at the primary hospital. Also, the investigators will calculate the financial burden related to ICU stay, inpatient stay at the hospital, readmissions, reoperations, and (expensive) treatment procedures and examinations performed as a consequence of a POPF-development.

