b)If glycerol is persistently < 400 μmol/l within the first 24 h the abdominal drains are removed at POD 1 (prerequisite: if no signs of bile, chylous or enteric stained fluid or at the surgeon’s discretion). After this, the patients are assessed and microdialysate results are reviewed. If microdialysate glycerol is persistently < 400 μmol/l over several PODs and the lactate-to-pyruvate ratio is < 50 combined with a lactate < 4 mmol/L, the patient is further mobilized and subsequently discharged. If the glycerol increases ≥ 400 μmol/l in 3 consecutive samples at a later stage, the patient is examined, and CT scan (or ultrasound/MRI) is performed (at the discretion of the surgeon). Further intervention undertaken will be as described above.

To improve adherence to the intervention protocols, the researchers arranged an introductory- and regular follow-up meetings with the surgical team during the ongoing trial. An allocated researcher was assigned for the daily contact with the surgical team. Study newsletters and bedside training for the ward nurses were regular events during the ongoing trial. To ensure participant adherence, the patients received daily follow-up by the research team during the hospital stay, and subsequently by telephone interview at 30 and 90 days after surgery.

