## Discussion

Pancreatic surgery is the only curative modality for pancreatic neoplasm. Despite better surgical techniques and improvement in postoperative care, the morbidity and mortality are still high. For the most part the morbidity is due to postoperative pancreatic fistula, which is regarded as the most threatening complication after pancreatic resection. This risk is also present for other diseases where a pancreatoduodenectomy is performed. Developing a POPF in a patient may have a great influence for the patient considering increased morbidity and mortality, but also may have a big impact for the hospital and the financial burden to the society. Diagnosing a POPF is traditionally based on clinical assessment together with blood samples and CT scans. These diagnostic tools reveal a POPF relatively late in the course of the natural development of this complication which may account for the high observed morbidity and mortality. Also, in a pancreatoduodenectomy an abdominal drain is inserted at the end of surgery and is commonly removed on POD 3. This can be a disadvantage in terms of fast mobilization after surgery. Using the microdialysis method the investigators are hoping to reveal a POPF at an earlier stage thereby initiate earlier interventions. Also, if microdialysis at POD 1 reveals no suspicion of a POPF, the abdominal drain is removed the POD 1, allowing for early mobilization. This in turn may reduce LOS at the hospital, morbidity, and mortality.

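### Complications are compared between arms over the hospital stay the trial aims to shorten, although they are recorded to POD 90; drain-fluid comparisons after POD 1 have a similar fault

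*Protocol article*

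**What the plan says.** All references are to the protocol article.

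- **Complication endpoint.** Table 1 (Objectives and endpoints), under the exploratory objective of comparing patients with and without a catheter, lists the "Number of patients with postoperative complications during total hospital stay in total and per complication". The abstract places the frequency of complications among the secondary endpoints.
- **What total stay is.** The primary endpoint row of Table 1 defines it as the index stay plus later surgery-related admissions at any hospital, transfers included. Statistical considerations assumes it is about 1.5 days shorter with microdialysis.
- **What is recorded.** Miscellaneous data to be collected says that complications, "as defined by the modified Clavien-Dindo classification, will be recorded until POD 90". Table 2 schedules them during admission, at discharge and on POD 30 and 90, with no distinction by arm.
- **Drain fluid.** The same exploratory objective compares amylase and bilirubin in drain fluid between arms. Table 2 samples drain fluid "At POD 1–3 and on indication thereafter if drain still in place". The intervention algorithm says that, if glycerol stays low over the first 24 hours, "the abdominal drains are removed at POD 1", subject to clinical provisos. The Discussion says that the drain "is commonly removed on POD 3". The section Abdominal drain fluid says the measurements are made in every patient and names no day.
- **Questionnaires.** They are taken preoperatively, around POD 3, and "at discharge ± 2 days from primary hospital + 30 and 90 days after surgery".
- **Fistula.** Occurrence of POPF, including a biochemical grade, serves Secondary 1, which evaluates predictive scores: "POPF defined according to the definition of the ISGPF". The between-arm time-to-leak endpoint is limited to grades B and C.

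**The concern.** A count of patients with an event is comparable between arms only if both arms are observed for the same time. Here the observation time is the length of stay, which is measured after randomisation and is what the intervention is meant to reduce. If microdialysis only sends patients home sooner, a complication that would have appeared on the last day or two in hospital drops out of the intervention count and stays in the control count. The trial could then report fewer complications when only the watching time has changed. Dichotomous endpoints are to be analysed by logistic regression on treatment group, and no allowance for the window is stated.

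Drain fluid has a parallel problem. After POD 1, intervention patients who still have a drain are disproportionately those with raised glycerol, whereas in controls glycerol plays no part in removal. A comparison of amylase or bilirubin on POD 2 or 3 therefore sets a selected subgroup against a much less selected one.

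**Working it through.** **The plan's own figure.** The sample-size table gives 84 per group for a 1.5-day reduction at power 0.932. Allowing for about 15% without the operation, 84 / 0.85 = 98.8, or 99, against the 100 per group stated. This agrees and is not in dispute. It leaves 100 × 0.85 = 85 evaluable patients per arm.

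**Inputs from the protocol.** Stay shorter by 1.5 days; overall morbidity 30% to 50% (Background); 85 per arm.

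**Assumptions, not in the protocol.** Control stay L of 8, 10 or 14 days; identical complication onset in both arms (no true effect); every patient in an arm has the same stay; at first, no late complication is recovered through readmission.

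**Pattern A, constant hazard over the stay.** With control risk p by day L, the risk observed in the intervention arm is 1 − (1 − p)^((L − 1.5)/L).

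- p = 40%, L = 10: 1 − 0.6^0.85 = 35.2%. Difference 4.8 points; OR = (0.352/0.648)/(0.40/0.60) = 0.82.
- p = 50%, L = 8 (largest): 1 − 0.5^0.8125 = 43.1%. Difference 6.9 points; OR 0.76.
- p = 30%, L = 14 (smallest): 1 − 0.7^(12.5/14) = 27.3%. Difference 2.7 points; OR 0.88.

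**Pattern B, early onset.** Let p be the eventual risk and m the mean onset time, 3 or 5 days. The risk seen by day t is p(1 − e^(−t/m)).

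- p = 50%, L = 8, m = 5 (largest): 39.9% against 36.4%. Difference 3.5 points; OR 0.86.
- p = 30%, L = 14, m = 3 (smallest): 29.7% against 29.5%. Difference 0.2 points; OR 0.99.

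**Chance of a significant result favouring microdialysis.** By the normal approximation, this is Φ((d − 1.96·SE0)/SE1), where d is the difference, SE0 the pooled and SE1 the unpooled standard error. For p = 40%, L = 10 under pattern A, SE0 and SE1 are both about 0.074, giving Φ(−1.32), or about 9%. The nominal value in that direction is 2.5%. The range is 6% to 15% under pattern A and 3% to 7% under pattern B.

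**Recovery through readmission.** In the 40%, 10-day case under pattern A, if a share r of missed complications leads to a surgery-related admission, 4.8 × (1 − r) remains: 2.4 points at r = 50%, 1.0 point at r = 80%, and none at r = 100%.

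**Fixed window.** Counted to POD 90 in both arms, the difference under no effect is 0 and the OR is 1 in every case.

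**Drain fluid.** No rate is needed. A POD 2 or 3 sample requires a drain. In the intervention arm, drain removal at POD 1 depends on glycerol; in controls it cannot. Table 2 limits later samples to patients with a drain, the algorithm takes drains out at POD 1 in some intervention patients, and Abdominal drain fluid speaks of all patients. The three statements are compatible only if the last means at least one sample, which it does not say.

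**The case against.** The strongest counter-argument is that total stay is not cut off at first discharge. It includes surgery-related readmissions at any hospital, so a serious late complication is usually still counted. This stands, and it reduces the bias. It does not remove it, because a complication managed without admission is not recovered.

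The calculation also shortens every stay equally. Complications prolong stay, so the patients who go home earlier are probably those at low risk, and many complications are likely to arise early. Both points favour the lower part of the range. The row is also labelled exploratory in Table 1, although the abstract calls complication frequency secondary.

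For drain fluid, Table 2 allows removal on POD 1–3 or later in general, and the POD 3 remark in the Discussion describes common practice. It cannot be assumed that nearly all controls keep a drain to POD 3. The dependence on arm remains, but its extent is unknown.

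Two stronger readings are tempting, and the protocol does not support them:

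- **That the questionnaire comparison as a whole is distorted.** Only the discharge assessment moves with length of stay. The preoperative, POD 3, POD 30 and POD 90 assessments are tied to surgery. The discharge tolerance of 2 days either way already exceeds the 1.5-day shift, and the protocol does not name discharge as the between-arm contrast.
- **That biochemical fistula will show a large spurious arm difference.** If a share q of intervention drains is out at POD 1 and those patients have relative risk k, a true rate b reads as b(1 − qk). With b = 20%, q = 30% to 70% and k = 0.5 to 1 (all assumed), it reads as 17% down to 6%. But no between-arm comparison of biochemical fistula is stated, so these figures describe an analysis that the protocol does not specify.

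**Conclusion.** The point holds for the complication endpoint: as worded, it can differ between arms when complications do not. Under the assumptions shown, the spurious difference is about 0.2 to 7 percentage points (OR 0.99 to 0.76) in favour of microdialysis before readmissions are allowed for, and smaller after. It is probably modest. It rests on a stay 1.5 days shorter and on stay and onset patterns that the protocol does not give.

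The point also holds, without a figure, for the exploratory between-arm comparison of drain amylase and bilirubin after POD 1. The discharge questionnaire and any later arm comparison of POPF occurrence are minor matters of wording. The primary endpoint is not affected.

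**What to change.** 1. In Table 1, define the complication endpoint as patients with a complication from end of surgery to POD 90 in both arms, in total and per type. The abstract and Table 1 should agree on whether it is secondary or exploratory.
2. Restrict the between-arm comparison of drain amylase and bilirubin to POD 1 samples, and describe later samples without comparing arms.
3. Reconcile Table 2, Abdominal drain fluid and the intervention algorithm on who is sampled and on which days, including whether the POD 1 sample is taken before any removal that day. This concerns the description of sampling, not the rule for removing drains.
4. Minor: base between-arm questionnaire contrasts on POD 3, 30 and 90 and report the discharge score descriptively. If POPF occurrence is compared between arms, use grades B and C, as the time-to-leak endpoint already does.

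The cost is wording in Table 1 and in the analysis plan, which is to be finalised before database lock. No new data are needed. The price is that drain fluid after POD 1 and, if POPF is compared, biochemical leak are no longer comparative outcomes.
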